# School-based mental health promotion in children and adolescents with *StresSOS* using online or face-to-face interventions: study protocol for a randomized controlled trial within the ProHEAD Consortium

**DOI:** 10.1186/s13063-018-3159-5

**Published:** 2019-01-18

**Keywords:** Mental health promotion, Prevention, School, Stress, Coping, Mental health literacy, Online intervention, Adolescents, Randomized controlled trial, ProHEAD

## Abstract

**Background:**

Schools are an ideal setting in which to promote health. However, empirical data on the effectiveness of school-based mental health promotion programs are rare, and research on universal Internet-based prevention in schools is almost non-existent. Following the life skills approach, stress management training is an important component of health promotion. Mental health literacy is also associated with mental health status, and it facilitates formal help-seeking by children and adolescents (C&A). The main objectives of this study are (1) the development and evaluation of an Internet-based version of a universal school-based health promotion program called *StresSOS* and (2) demonstrating non-inferiority of the online setting compared to the face-to-face setting. *StresSOS* aims to improve stress management and mental health literacy in C&A.

**Methods/design:**

A school-based sample of 15,000 C&A (grades 6–13 and older than 12 years) will be recruited in five regions of Germany within the ProHEAD Consortium. Those with a screening result at baseline indicating no mental health problems will be invited to participate in a randomized controlled trial comparing *StresSOS* online to an active online control condition (Study A). In addition, 420 adolescents recruited as a separate school-based sample will participate in the *StresSOS* face-to-face intervention. Participants in both intervention groups (online or face-to-face) will receive the same eight treatment modules to allow for the comparison of both methods of delivery (Study B). The primary outcome is the number of C&A with symptoms of mental health problems at a 12 months follow-up. Secondary outcomes are related to stress/coping (i.e., knowledge, symptoms of stress, coping resources), mental health literacy (knowledge and attitudes toward mental disorders and help-seeking), program usage patterns, cost-effectiveness, and acceptability of the intervention.

**Discussion:**

This study represents the first adequately powered non-inferiority trial in the area of school-based mental health promotion. If online *StresSOS* proves efficacious and non-inferior to face-to-face delivery, this offers great potential for health promotion in youths, both in and outside the school environment.

**Trial registration:**

German Clinical Trials Register, DRKS00014693. Registered on 14 May 2018.

**Electronic supplementary material:**

The online version of this article (10.1186/s13063-018-3159-5) contains supplementary material, which is available to authorized users.

## Background

Mental health problems in childhood and adolescence are key health issues (see, e.g., [1]). In children and adolescents (C&A) mental health problems present a burden for individuals, their families, and the social environment that may persist over the lifespan. Greater efforts for mental health promotion and prevention interventions are desperately needed. Schools are an ideal setting in which to promote health [2]. The school is the place where C&A spend a lot of their time. It influences the cognitive, social, and emotional development of C&A for years and contributes to the stabilization of behavioral habits (including health behaviors). School is the place where most young people can be reached, and it provides access to cohorts of C&A as a whole within a region. It establishes an organizational framework for group-related interventions and their evaluations [3]. Yet studies documenting health promotion activities at schools (e.g., [4, 5]) that focus on the promotion of mental health and wellbeing are the exception, and most evaluated interventions have been developed and implemented in the USA [6].

School-based health promotion or prevention programs often follow a universal approach and are delivered to all individuals of a cohort. Meta-analyses have identified a range of positive small to moderate effects of school-based mental health promotion with large impact [6]. The “Life Skills” training [7, 8] is a prototypical health promotion approach that focuses on enhancing social and personal skills to enable individuals to deal effectively with the demands and challenges of everyday life. Core life skills include communication, decision-making and problem-solving, and coping with emotions and stress (see the World Health Organization (WHO) definition [7]). How individuals cope with stressful situations strongly influences the impact stress has on adjustment and health [9, 10]. Stress involves a person’s response pattern to particular events (i.e., stressors) that disturb the individual’s equilibrium and tax or exceed his or her ability to cope. Thus, stressors and coping are important mental health factors. Transactional definitions [10] point to the degree to which situations are perceived as taxing or exceeding resources and endangering a person’s wellbeing, not solely to the situation itself. Consequently, an individual’s appraisal of events or situations (e.g., demands of school; conflicts among family, friends, or peers) and of his/her resources is important. Coping refers to changing cognitive and behavioral efforts to manage specific demands that are appraised as taxing or exceeding one’s resources [10]. In past years, school-based stress prevention training programs (mostly face-to-face) have been developed for C&A (see, e.g., [11–13]). Programs typically focus on knowledge about stress and strategies to deal with it (e.g., problem-solving, alternative/positive thinking strategies, relaxation techniques, social support seeking). Evidence supports benefits from the intervention (e.g., increased knowledge, more adaptive coping). In their meta-analysis on school-based stress management programs (19 studies included), Kraag et al. [14] tentatively conclude that school programs targeting stress/coping are effective in reducing stress symptoms and enhancing coping skills (see also [6, 15]). Yet, future research should be methodologically stronger (e.g., with regard to outcome measures or follow-up data).

Internet-based interventions hold many advantages; for example, they can save resources, such as teachers’ classroom time or researchers for program delivery, and enhance reach. They are easily accessible for C&A, who spend a lot of time using electronic media [16]. Among others, one function of electronic media use, including the Internet, is to help a person cope with stress [17]. Reviewing the effectiveness of online mental health promotion and prevention interventions for C&A, Clarke et al. [18] identified only two online stress management interventions [19, 20]. Both types of training correspond in content with face-to-face stress prevention programs (i.e., providing knowledge about stress and strategies to deal with stress). The authors reported improvements in knowledge about stress and coping and showed first indications for more adaptive coping strategies.

With the aim of coping with stressors or strains in the future, mental health literacy (MHL) is also an important concept. Adolescence is a period of significant risk for mental disorders [21]. However, if mentally ill, a large proportion of adolescents fail to obtain the needed mental health care. A recent review (based on 22 studies [22]) of perceived barriers and facilitators for mental health help-seeking in young people showed that perceived stigma and embarrassment, problems recognizing symptoms, and a preference for self-reliance were the most important barriers. However, perceived positive past experiences, social support, and encouragement from others were identified as facilitators of the help-seeking process. The review concluded that strategies for improving help-seeking in C&A should focus on improving MHL and reducing stigma. MHL has been defined as “knowledge and beliefs about mental disorders which aid their recognition, management or prevention” [23]. Following Jorm [23], MHL encompasses knowledge that is linked to the possibility of action to benefit one’s own mental health or that of others including knowledge of how to prevent mental disorders, recognition of when a disorder is developing, knowledge of help-seeking options and treatments available, knowledge of effective self-help strategies for milder problems, and first aid skills to support others who are developing a mental disorder or are in a mental health crisis. School-based MHL programs address basic concepts of mental health, provide strategies for help-seeking, or include activities for stigma reduction toward mental illness. However, programs are heterogeneous with regard to the focus of the interventions, duration, and dose (for a review, see [24]). For example, the HeadStrong intervention [25] is a universal, curriculum-based program on MHL, stigma, help-seeking, psychological distress, and suicidal ideation. Classroom activities are delivered by teachers over a period of 5–8 weeks in five modules (e.g., “Mood and mental wellbeing”, “Reaching out – helping others”). *The Guide* resource (teenmentalhealth.org) consists of six modules covering stigma and mental illness, understanding mental health and mental illness, information on specific mental illnesses, experiences of mental illness, help-seeking, and the importance of mental health [26]. Reviewing the effectiveness of school-based MHL programs (Cochrane criteria applied, 27 studies included), Wei and colleagues [24] state that even if most studies report improved knowledge (12 of 15 studies), changes in stigmatizing attitudes (14 of 21 studies), and/or enhanced help-seeking behavior (8 studies, of which 5 studies investigated attitudes toward help-seeking; results were mixed for different sources), the quality of the evidence is low. Methodological weaknesses include, but are not limited to, the lack of randomized controlled trials (RCTs), missing control for confounders (e.g., age, gender, mental health status), and the lack of validated measures. In addition, former reviews on school-based MHL interventions [27, 28] primarily criticize the quality of research designs (e.g., small sample sizes, lack of follow-ups). Regarding Internet resources, there are various websites to improve youth MHL skills (e.g., mindcheck.ca, foundrybc.ca; see [29]). Preliminary pilot data support the idea that brief Internet-based MHL interventions improve knowledge and help-seeking attitudes [30]. The topics covered were, for example, depression, anxiety, and suicide.

To summarize, in terms of resource promotion and empowerment among C&A, both coping skills and MHL are powerful resources. C&A benefit from a broad spectrum of coping strategies to alter a specific stressful situation (e.g., problem-solving, instrumental support seeking) or adjust to the stressor (e.g., emotion regulation, emotional support seeking) to enhance individual strengths to manage challenges and demands. MHL enables self-help strategies for milder problems and, for example, first aid skills to support others. Preliminary evidence on universal school programs targeting stress/coping or MHL (mostly face-to-face) tentatively supports benefits for mental health in C&A. However, existing reviews on the effectiveness of stress/coping or MHL preventions clearly document methodological weaknesses and conclude that there is a need for more research targeting stress/coping and MHL utilizing sound designs (e.g., RCTs with pre-test, post-test, follow-up, adequate sample size, and outcome measures). Advantages of Internet-based programs are evident (e.g., personnel and time resources, accessibility, reach, attractiveness, target-group specificity); however, research is still in the early stages.

### Objectives

The aim of the study is the development, implementation, and evaluation of a health promotion program named *StresSOS* addressing stress management and MHL. It is planned to investigate the efficacy of Internet-delivered *StresSOS* compared to an active online control condition (Study A) and non-inferiority of *StresSOS* online delivery to *StresSOS* face-to-face delivery (Study B) with regard to a reduction of new incidence of mental health problems in C&A. The primary hypothesis is that significantly fewer C&A in the *StresSOS* group will transit from the “healthy” group to the “high-risk” or the “mental health problems” group at 12 months follow-up, when compared to a control group receiving an online program on healthy nutrition. Further, we will explore for whom the program is most effective (e.g., child demographics). The programs’ acceptability will be analyzed to identify factors supporting or hindering the implementation of the Internet-based or the face-to-face prevention program at schools. In addition, data will be collected on the cost of interventions and compared to the study outcomes to determine the cost-effectiveness ratio of interventions.

## Methods/design

### Design

ProHEAD is a longitudinal study with three school-based screenings at intervals of 12 months assessing mental health problems in C&A. Further, it is an interventional study, allocating C&A to different programs tailored to their individual needs and evaluating the efficacy and cost-effectiveness in a randomized controlled design (see also https://www.prohead.de/). The *StresSOS* trial is an RCT within the ProHEAD Consortium. Healthy adolescents will take part in either a face-to-face *StresSOS* intervention at school, in a *StresSOS* online intervention at home, or in an online control group. Participants in both intervention groups (online or face-to-face) will receive the same treatment modules. The efficacy of the online program will be investigated as compared to the control condition (Study A) and non-inferiority of online delivery compared to face-to-face delivery (Study B); see Fig. 1. Additional file 1 provides the completed Standard Protocol Items: Recommendations for Interventional Trials (SPIRIT) checklist.

**Fig. 1 Fig1:**
[figure not shown]
StresSOS trial intervention scheme and trial flow. Note: Participants will complete the ProHEAD baseline screening and 1 and 2 year follow-up assessments within the ProHEAD Consortium. In addition, assessments within the *StresSOS* trial will be conducted at baseline and post-intervention (8 weeks after onset of intervention)

### Recruitment

Participants for the Internet-delivered *StresSOS* (and the corresponding online control group) will be recruited within the ProHEAD Consortium via schools in five regions of Germany (Hamburg, Heidelberg, Leipzig, Marburg, Schwäbisch Gmünd). Details on the recruitment can be found in Kaess et al. [31]. Participants for the face-to-face *StresSOS* program will be recruited as an additional sample via schools in the region of Schwäbisch Gmünd, Germany.

### Enrollment and randomization

Permission to contact schools within the regional districts of all five recruiting study sites (Hamburg, Heidelberg, Leipzig, Marburg, Schwäbisch Gmünd) will be requested from federal authorities. A total list of schools in the regional districts will be acquired. Eligible schools will be contacted and informed, in random order, about the possibility to participate, until the prospected sample size is reached (in total *N* = 15,000 C&A). Following the baseline screening, healthy C&A (not fulfilling allocation criteria for any other ProHEAD program; see [31–34]) will be invited to participate in the *StresSOS* online program. C&A will receive an email including information about the trial and access details for the baseline assessment within the *StresSOS* trial. After completing this assessment, participants will be randomized with equal probability (in a 1:1 ratio) to the online *StresSOS* program and the online control group (online program on healthy nutrition). The allocation will be randomized, stratified for gender and school type. Randomization will be conducted externally and will follow a permutated block design with variable, randomly arranged block sizes. Following randomization, participants will be contacted informing them about their allocation to the respective intervention group and will receive access details for the specific online program.

In the face-to-face *StresSOS* program, the entire class will be invited to participate in the trial. Parallel to the online trial, eligible schools will be contacted and informed in random order about the possibility of participating in the program. Blinding is not possible. Participating C&A and experts are not unaware of the interventional procedure. However, assessments are based on self-report and take place within the school-based screening, which helps to avoid biased assessment of results.

### Inclusion and exclusion criteria

C&A from participating schools who are in grades 6–13 and older than 12 years and who provide both written informed consent forms (children, adolescents and parents) are invited to participate in the ProHEAD baseline screening. Following the baseline screening, C&A will be identified as currently either “healthy”, “high-risk” (including sub-threshold mental health problems and diverse health-risk behaviors), or having “mental health problems” (which includes clinically relevant levels of psychopathology and/or indicators of threat to self and others). Based on these screening profiles, C&A will be allocated to one of the five ProHEAD online trials: increasing help-seeking in C&A with general mental health problems [31]; reducing eating disorder symptoms [32]; reducing at-risk alcohol use [33]; reducing depressive symptoms [34]; promoting mental health in healthy C&A (this *StresSOS* RCT). That is, healthy C&A without mental health problems and without at-risk mental health symptoms as assessed in the school-based ProHEAD screening not fulfilling allocation criteria for the other four ProHEAD online programs [31–34] are invited to participate in the *StreSOS* trial. Further inclusion criteria are sufficient German language skills and Internet access. Criteria for the allocation of participants to the five individual ProHEAD trials (i.e., this *StresSOS* RCT and the other four programs [31–34]) are based on the latest scientific evidence. However, this is the first time that the overall algorithm will be applied on a consortium-wide basis simultaneously screening for various mental health problems. Therefore, an intermediate data analysis will be conducted following completion of 10% of the screening assessments (*N* = 1500 C&A) in order to determine the actual allocation ratio to the five ProHEAD trials and to adjust the screening algorithm if necessary.

### Participants’ incentive

Participants receive no direct financial compensation for participating in the school-based assessments. Among all participating students, a draw will be conducted, awarding vouchers for online shopping portals (20€ in value) to 5% of the participants.

### Intervention

All interventions (online and face-to-face) comprise eight weekly sessions. Each session provides knowledge and information referring to the session’s main issue, reinforces content by illustrating particular examples, tests participants in a playful manner (e.g., with quizzes and exercises on the session’s topic), and fosters transfer to daily life with a weekly homework assignment aiming to increase self-management skills.

### *StresSOS* (online or face-to-face)

The *StresSOS* program focuses on stress/coping and MHL. It teaches coping skills (e.g., problem-solving, cognitive reconstruction, relaxation techniques, seeking support), the connection between thoughts, feelings, and behaviors, and concepts about mental health/illness and help-seeking. See Table 1 for a content overview of the *StresSOS* sessions (online and face-to-face). The *StresSOS* program is based on the life skills approach, especially stress prevention programs (e.g., [11, 12]) and MHL programs (e.g., [25, 26]).

**Table 1 Tab1:** *StresSOS* module content

Module number and content	Content overview
1. The basics of stress and wellbeing	What is stress? How does stress affect the body? How does stress occur? Is stress a disease?
2. Managing stress: problem-solving	When do I get stressed? What can I do if I find myself in a stressful situation? I have a problem — how can I solve it?
3. Helpful thoughts	Stress occurs in the head — why thoughts play a role. Relationship between thoughts, feelings, and behavior. My helpful thoughts and feelings — my hindering thoughts and feelings. How can I change my thoughts and expectations?
4. Time to chill out and relax	What happens in the body during relaxation? What possibilities for balance and recreation are there? What are relaxation methods?
5. Upward spirals of positive emotions	Spiral of emotions — up or down? What is the spiral of positive emotions? What makes me feel good? How can I influence my emotions? What do positive feelings and stress management have in common?
6. Seek support and talk	What is social support and why is it so important? Social support — a give and take. Whom can I contact if I feel I can’t cope on my own? How can I make social contacts? How do I express socially competent and self-confident behavior?
7. Mental health and mental illness	What is mental health? What are risk factors and protective factors? Stress and mental illness — what’s the difference? Mental illness in adolescents — is this an issue at all? How can I help others?
8. A glimpse into the future — finding one’s own goals	Finding the appropriate goals. Why are goals important? What do goals have to do with stress and wellbeing? Why can thinking about goals be helpful?

The *StresSOS* face-to-face program is a classroom-based intervention, administered by experts (advanced students, mental health professionals). One weekly session lasts 90 min. A variety of teaching methods will be included (e.g., presentations, group discussion, group activities, role play, video presentations, games, quizzes, answer sheets, homework). The *StresSOS* online program will be completed by C&A autonomously (e.g., from their computer at home). A weekly session takes approximately 20–90 min according to individual needs and preferences. The program contains information and psycho-educational materials, interactive online training, quizzes, and exercises on the session’s topic. An individualized monitoring and feedback module is implemented. Once a week participants will receive an email that reminds them about the upcoming session. Via a link in the email they can access an online monitoring questionnaire, which asks them whether they have completed their “homework” (“Your turn! Give it a try”) and whether they liked it. The following individualized feedback will reinforce positive behaviors and offer suggestions and recommendations in case C&A did not complete their homework or did not experience the task as helpful or good. A group chat moderated by an expert takes place once a week. C&A are invited to join the chat on a voluntary basis and have the opportunity to ask questions of the expert or discuss their experiences within the program with their peers. Finally, the program contains a news blog. Moderators frequently upload information to the news blog and provide up-to-date news about the topic.

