### Sample size calculation

In the control condition, 30% transitions from “healthy” to “at-risk” are expected. Further, it is anticipated that participation in *StresSOS* (online or face-to-face) will prevent 50% of these transitions, i.e., reduce the transitions to 15%. The sample size calculation is primarily based on the non-inferiority trial (Study B). Assuming equal efficacy for online and face-to-face delivery of *StresSOS* (i.e., 15% transition to “at-risk”), a non-inferiority margin δ = 5%, and an allocation ratio of 5:1, 2920 participants (2500 in the online and 420 in the face-to-face condition) need to be included in Study B to test non-inferiority with 80% power at α = 5% (Z-test). For Study A, the proposed sample size will allow one to assess the assumed group differences precisely (95% confidence interval (CI) +/− 2.3%); i.e., it allows one to test clinical significance of the efficacy of online *StresSOS* (between-group difference > 10%) with more than 95% power. The sample size may be larger, as all C&A who do not meet the inclusion criteria of the other four ProHEAD trials for C&A with (sub-threshold) mental health problems [31–34] are included. Even if the proposed sample size is reached, the program will still be offered to “healthy” C&A.

Based on previous experiences in school-based settings, there may be an expected loss to follow-up rate of 15% for the face-to-face sample [36] and 25% for the program-specific assessments of the online sample. Based on the literature [19] and the experiences within the consortium, the expectation is that about 33% of the participants in the online *StresSOS* condition will be compliant and work through the modules as expected, 33% will utilize about half of the modules, and 33% will log in only once.

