#### Study B

Non-inferiority [56] of online delivery of *StresSOS* will be tested against the null hypothesis H0: Difference (% transitions face-to-face – % transitions online) < 5% (Z-test, α = 5%). Non-inferiority is assumed if the upper limit of the 95% CI of the empirical group difference is less than 5% (CI inclusion approach). Propensity score weighting methods will be applied to control for potential confounders between the online and the face-to-face condition [57]. The covariates taken into account for the propensity score procedure will be, for example, psychological strain, coping skills, age, gender, and type of school. Tests will be based on ITT principles; missing values will be imputed.

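### Study B sizes and tests the class-based face-to-face arm as if its pupils were independent, so its confidence interval is too narrow and its stated power too high for a valid test

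*Protocol article*

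**What the plan says.** All places are in the protocol article.

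- **Delivery, face-to-face** (StresSOS (online or face-to-face)): the "face-to-face program is a classroom-based intervention, administered by experts (advanced students, mental health professionals"), with group discussion, group activities and role play among the methods.
- **Recruitment, face-to-face** (Enrollment and randomization): "the entire class will be invited to participate in the trial". Under Recruitment, these participants "will be recruited as an additional sample via schools in the region of Schwäbisch Gmünd, Germany".
- **Delivery, online** (StresSOS (online or face-to-face)): the "online program will be completed by C&A autonomously (e.g., from their computer at home").
- **Sample size** (Sample size calculation): "Assuming equal efficacy for online and face-to-face delivery", with 15% transitions in both arms, "a non-inferiority margin δ = 5%, and an allocation ratio of 5:1, 2920 participants (2500 in the online and 420 in the face-to-face condition") are needed "to test non-inferiority with 80% power at α = 5% (Z-test"). Expected loss is 15% face-to-face, and 25% online for the program-specific assessments.
- **Analysis** (Statistical analyses, Study B): a Z-test at α = 5%, with non-inferiority declared when the upper 95% CI limit is below 5%. "Propensity score weighting methods will be applied to control for potential confounders between the online and the face-to-face condition". The example covariates include type of school, but not the class or the individual school.

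For Study B the article mentions no intraclass correlation, design effect, class or school effect, or robust variance.

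**The concern.** Pupils who are recruited as a class and go through eight sessions together are unlikely to have independent outcomes a year later. The primary outcome draws on alcohol use, mood and peer problems, which classmates can be expected to share. Positive correlation makes the true variance of the face-to-face proportion larger than the binomial variance behind a Z-test on proportions.

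In a non-inferiority test the consequence runs in the harmful direction. An understated standard error pulls the upper confidence limit below the margin too easily, so the typical mistake is to claim that online delivery is no worse when it is. Non-inferiority is one of the two main objectives in the Abstract, and the Discussion describes the trial as adequately powered for it.

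**Working it through.** **Inputs from the article.** Transition rate p = 0.15 in both arms; margin 0.05; 420 face-to-face and 2500 online; loss 15% and 25%. The sidedness of α is not stated. A two-sided 95% CI corresponds to one-sided 2.5%, so both that and one-sided 5% are shown. The difference is taken as online minus face-to-face.

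**Assumptions (not in the article).** m = 12 to 25 analysed pupils per class; ICC = 0.01 to 0.05; online pupils independent; no extra variance from the propensity weights.

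**1. The plan's own figure.** Face-to-face n = (z₁₋α + z₀.₈)² × p(1−p) × (1 + 1/k) / 0.05², for independent pupils.
- k = 5, one-sided 5%: 379 + 1895 = 2274. After dividing by 0.85 and 0.75: 446 + 2527 = 2973.
- k = 5, one-sided 2.5%, no loss: 481 + 2405 = 2886.
- Power with 420/2500: 84.4% (one-sided 5%) or 75.7% (one-sided 2.5%). With 357/1875 after the stated losses: 78.2% or 67.9%.

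The stated 2920 and 80% are reproduced closely, though not exactly, and only by formulas for independent pupils. At the actual split (2500/420 = 5.95) the unclustered need at one-sided 5% is 369 face-to-face pupils, and 369/0.85 = 435. So 420 contains no hidden clustering allowance.

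**2. Where the variance lies.** p(1−p) = 0.1275. Face-to-face: 0.1275/420 = 0.000304. Online: 0.1275/2500 = 0.000051. Share: 0.000304/0.000355 = 86%. The large online arm cannot dilute the clustering.

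**3. Formulas with clustering.** DE = 1 + (m−1) × ICC, applied to the face-to-face variance only.
- Power of an adjusted test = Φ(0.05/SE − z₁₋α), with SE² = 0.1275 × DE/n_f + 0.1275/n_o.
- Error of the unadjusted test at the margin (online 20%, face-to-face 15%) = Φ(−z₁₋α × SE_naive/SE_true), with variances 0.1275/420 and 0.16/2500, the first multiplied by DE in SE_true.

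**4. One case in full: m = 20, ICC = 0.02.** DE = 1 + 19 × 0.02 = 1.38; effective n = 420/1.38 = 304. SE² = 0.1275 × (1.38/420 + 1/2500) = 0.000470, SE = 0.0217. Power = Φ(2.307 − 1.960) = 64%, or Φ(2.307 − 1.645) = 75%. SE_naive/SE_true = 0.01917/0.02198 = 0.872. Error = Φ(−1.710) = 4.4%, or Φ(−1.435) = 7.6%.

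**5. Range.** Each pair is 95% CI rule / one-sided 5%. Error is for 420/2500.

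| m, ICC | DE | Effective n of 420 | Error, unadjusted test | Power, adjusted test, 420/2500 | Power, adjusted test, 357/1875 |
|---|---|---|---|---|---|
| independent | 1.00 | 420 | 2.5% / 5.0% | 76% / 84% | 68% / 78% |
| 12, 0.01 | 1.11 | 378 | 3.0% / 5.8% | 72% / 81% | 64% / 75% |
| 25, 0.01 | 1.24 | 339 | 3.7% / 6.6% | 68% / 78% | 60% / 71% |
| 20, 0.02 | 1.38 | 304 | 4.4% / 7.6% | 64% / 75% | 56% / 68% |
| 12, 0.05 | 1.55 | 271 | 5.2% / 8.6% | 59% / 71% | 52% / 64% |
| 25, 0.05 | 2.20 | 191 | 8.2% / 12.2% | 46% / 59% | 40% / 53% |

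With 420/2500 the correct 95% CI half-width grows from 3.7 points (independent) to 5.3 points (m = 25, ICC 0.05), which is wider than the margin itself.

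**6. Simulation check.** Beta-binomial classes of 20, 100,000 runs, ICC 0 against 0.02: error rises from 2.0% to 3.6% (95% CI rule) and from 4.2% to 6.7% (one-sided 5%). The levels are slightly lower than by formula; the direction is the same.

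**The case against.** **The size depends on two figures the article does not give.** This stands. Invited classes shrink through consent by pupil and parents, the restriction to healthy pupils and 15% loss, so 25 analysed pupils per class is a high value. At m = 12 and ICC 0.01, with no loss and one-sided 5%, an adjusted test still has 81% power. A reader might infer that 80% power is unattainable under any assumption; the article does not support that. After the stated losses, however, the same mild case gives 75%, or 64% under the 95% CI rule.

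**Adjusted power is not the power of the planned test.** Correct. Over the assumed range, the unadjusted Z-test on clustered data with 420/2500 has about 75% to 69% power (95% CI rule) or 83% to 76% (one-sided 5%). It loses less because it trades power for false non-inferiority. The inflated error and the low power therefore belong to two different analyses.

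**The error stays under the stated 5%.** Under the 95% CI rule this is so until the design effect reaches about 1.5. It still exceeds the 2.5% that a two-sided 95% CI implies.

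**The variance estimator belongs in the analysis plan.** Partly right. A Z-test on a weighted estimate does not exclude a robust standard error, and an unseen analysis plan may specify one. It could not make the stated sample size and power, fixed without clustering, right for that test.

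**Stronger readings.** One might infer that only a few schools take part, or that one leader teaches each class. The article gives no number of schools or classes, and says only that experts deliver the sessions. Nor does it give anything from which to calculate how much variance the propensity weights add. The point needs none of these. The 25% online loss is stated for the program-specific assessments, so 1875 may be too low for the primary outcome; with 357/2500 the independent power at one-sided 5% is 79.7% rather than 78.2%, a small change.

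**Conclusion.** The point holds. The face-to-face arm is clustered by recruitment and by delivery, it carries about 86% of the variance, and the stated sample size and power make no allowance for clustering. For any positive ICC the interval from an unadjusted Z-test is too narrow and false non-inferiority becomes more likely. That direction is certain. The size is conditional on 12 to 25 analysed pupils per class and an ICC of 0.01 to 0.05 (design effect 1.11 to 2.20), with online pupils taken as independent: error up to about 8.2% instead of 2.5%, or 12.2% instead of 5%, and adjusted power with the stated numbers down to 46% or 59%. At the mild end the effect is modest before loss to follow-up. The supported conclusion is that the stated 80% does not describe a test that respects the class structure, not that any one of these power figures is the true one.

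**What to change.** 1. Record class and school identifiers for face-to-face pupils, and school for online pupils.
2. Take the upper confidence limit from a propensity-weighted risk-difference model with cluster-robust variance. Use the class as cluster (online pupils as singletons or grouped by school), a small-sample correction and a t reference distribution. Add a school-level sensitivity analysis.
3. Restate Study B power with a design effect on the face-to-face arm, over a declared range of ICC and analysed pupils per class, at the error level that the 95% CI rule implies and after expected losses.

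The cost is two identifiers, revised analysis wording, a wider interval and a less favourable stated power. No additional enrolment is required, but the change does not by itself restore 80% power, and the restated figure should say so.
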